##### Data collection

Data are collected by postal questionnaire at recruitment (T0), then 4 months (T1) and 8 months post-recruitment (T2) (see Fig. 2). Clinical and treatment data (cancer stage, grade, date of diagnosis, and treatment received) are collected from medical records. If a participant dies during their involvement with the study, it is ascertained whether the death was due to prostate cancer.

**Fig. 2 Fig2:**
[figure not shown]
Study flow

##### Recruitment

Men were recruited to the comparator group between September 2014 and June 2015, and to the Programme group between April 2015 and February 2016, with data collection completed in December 2016.

Men attending a clinic appointment who met the eligibility criteria for the evaluation were initially approached by clinical staff or a research nurse, to introduce the evaluation and to ask for consent for their contact details to be passed to the research team. Men who consented to contact were sent, by post, an introductory letter, a patient information sheet, consent form, baseline questionnaire and a freepost envelope for return of the completed documents.

##### Outcome measures

The evaluation is comparing the Programme with standard care across a number of different outcomes; a series of validated patient reported outcome measures are being used (see Table 1), to reflect multiple outcomes of interest relevant to the theoretical model underpinning the Programme [21].

**Table 1 Tab1:** Outcome measures

Outcome measures at T0, T1 and T2			
Description of outcome	Measure used	Description of measure	Psychometric/biometric properties of measure
Unmet need (primary outcome)	Cancer Survivors’ Unmet Needs Measure, (CaSUN) [22]	35 questions regarding unmet need in 5 domains of existential survivorship; comprehensive cancer care; information; quality of life; relationships. Additional 6 questions about positive life changes and space for free comments The unmet need questions can be scored as individual items or as scores of unmet and total need, and/or strength of need.	Due to reported difficulty with the five point response format used by the CaSUN, this study has followed others in using a simplified four point response format [35]
Health status	EQ5D-5 L [24]	5 questions addressing mobility, self-care, daily functional status, pain and/or discomfort, anxiety and/or depression; 5 point Likert scale; converts to single index value for calculation of quality-adjusted life years; utility estimates have been provided for cancer patients [36].	There is support for the scale’s reliability and validity when used with cancer patients [36]
Prostate cancer health related quality of life	Expanded Prostate Cancer Index Composite Short Form (EPIC-26) [37]	26 questions in 5 domains of urinary incontinence; urinary irritative/obstructive; bowel; sexual; and hormonal; 4 and 5 item Likert scales; individual items are scored as a total on a 0–100 scale.	Good internal consistency (Cronbach’s alpha ≥ 0.70 for each domain) and test-retest reliability (*r* ≥ 0.69 for each domain) [38].
General cancer related quality of life	Functional Assessment of Cancer Therapy Scale - General (FACT-G) [39]	28 questions in 4 domains of physical wellbeing; social/family wellbeing; emotional wellbeing; functional wellbeing. 5 item Likert from ‘not at all’ to ‘very much’; provides domain scores and a total score.	Reliability and validity have been shown to be high [39]
Psychological well being	General Health Questionnaire (GHQ-12) [40]	Measure of current mental health using 12 questions and 4 point Likert scale that provides an overall total score.	The GHQ-12 has been extensively evaluated and shows good validity and reliability [41].
Activation to self-manage	Patient Activation Measure (PAM®) [42]	The short form comprises 13 questions answered on 5 point scale, from ‘disagree strongly’ to ‘agree strongly’ plus N/A; scores from a minimum of 10 responses into one of 4 levels of activation.	The short form version has been shown to be reliable and valid [43]
Worry about cancer recurrence	Adaptation of the Worry of Cancer Scale [44]	2 questions to measure frequency and degree of intrusiveness of worry about cancer recurrence; Likert scales of 0–10 and 0–4; calculates score of 0–20	No psychometric data for the modified version, but the original scale performed well [44]
Health behaviours - diet	Adaptation of the Fruit and Vegetable Screening Measure for Adolescents [45]	Rating fruit and vegetable consumption in a typical day, as two separate items; response adapted to include 5 or more portions, to be in line with current guidance	The measure has shown to be reliable and valid [45]
Health behaviours – physical activity	Leisure Time Exercise Questionnaire [46]	Measure of leisure time physical activity as mild, moderate and strenuous activity, plus activity to work up a sweat as number of units of 15 plus minutes per week. A total score is calculated, which can be used to classify respondents as active, moderately active and insufficiently active [47]	Reliability and validity of the measure has been shown [46] The classification system has been validated or use with cancer survivors [48]
Health behaviours - smoking	Developed for this study, drawing on measurement of these items in health promotion work.	1 question to measure current smoking behaviour	
Health behaviours - alcohol	Developed for this study, drawing on measurement of these items in health promotion work.	1 question to record frequency of current alcohol consumption	
Outcome measures at T1 and T2			
Health service use	Developed for this study, based on a previous evaluation at the University of Southampton [16]	15 questions about contact with health and community services for prostate cancer related issues and patient costs related to prostate cancer	
Satisfaction with follow-up care	Developed for a previous evaluation at the University of Southampton [16]	11 questions and space for free text comments regarding experience and acceptability of follow-up care	
Other variables			
Demographic characteristics	Date of birth, ethnicity, marital status, level of education, employment status, housing status, caring responsibilities, computer use.		

Measures of general health status, physical symptoms, cancer specific quality of life, unmet needs, psychological wellbeing, worry about cancer recurrence, activation for self-management, and general health behaviours are being collected at T0, T1 and T2 time points. In addition, questions about health service use and satisfaction with follow-up care are included in the T1 and T2 questionnaires. Socio-demographic characteristics are also collected. The primary outcome is unmet need, measured with using the Cancer Survivors Unmet Needs measure [22].

##### Sample size calculation

The sample size was calculated to achieve at least 90% power in two sided tests for variables which achieve a moderate intervention effect (0.3 or larger). This would require a sample of 235 participants per group and we therefore aimed to recruit around 300 men to each arm of the study, allowing for 20% being lost to follow-up by the 8 month assessment.

##### Data analysis

Data analysis will follow a pre-specified data analysis plan. Analyses will be conducted on an ‘intention to treat’ basis. We will first describe the baseline characteristics of participants at time T0 within each group and will compare clinical and demographic characteristics and outcome measure scores of the two groups. The same comparisons will be made with baseline data between those continuing to four and 8 month follow-up and those lost to attrition.

A regression analysis will be conducted for each of the outcome measures at the 4 month and 8 month time points separately, controlling for study site, the outcome in question if available at T0, and baseline co-variates including age, type of treatment, educational attainment, time since diagnosis, domestic status, co-morbidity, employment status, and ethnic status. If other factors differ between groups at baseline, additional controlled analyses will be carried out.

We will also estimate a mixed model including outcome at four and 8 months simultaneously, including an interaction to give separate estimates of the Programme versus standard care comparison at each follow-up point.

Finally, we will investigate whether there are any distinct subgroups for whom the intervention is effective. Guided by existing literature to indicate likely subgroup effects, separate regression analyses will be conducted for older versus younger men, men with and without co-morbidities, and men with higher and lower levels of deprivation. We will address subgroup analyses within the context of regression modelling (either linear or logistic). Interaction terms between each specified dichotomous factor (indicating subgroups) and the Programme versus standard care factor will be examined. Where interaction terms achieve statistical significance (at the 5% level), we will examine separate Programme versus comparator group estimates for each subgroup. All subgroups analyses will be considered exploratory in nature.

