## Discussion

The TrueNTH Supported Self-Management and Follow-up care Programme implements an integrated supported self-management and remote monitoring model of follow-up care within secondary care. The Programme aims to address contemporary problems with clinic capacity, but also to offer men a more tailored follow-up care experience that addresses their individual needs. While other alternatives to the clinic based model of post treatment care continue to be tested (for example, [30–32]), this Programme offers an alternative which maintains specialist oversight and input.

The Programme was funded as a service improvement initiative with accompanying evaluation. The evaluation takes a pragmatic approach [20], seeking to answer questions about effectiveness of the model within an everyday clinical setting, and also to provide information on the practicalities of implementing and sustaining such a model. Such information should provide relevant and useable conclusions for local decision makers considering implementation of a similar model in their setting [20].

There are a number of limitations to the study design. First, the use of a non-randomised comparator group represents a reduction in the ability of the study to attribute outcomes to the Programme, though the inclusion of a baseline measurement helps to address this issue, allowing for statistical adjustment of known confounders [33]. Second, men will be followed up for a period of 8 months, meaning that the study will only be able to comment on outcomes over this time period and not over a longer term [21].

Within the context of the rising number of cancer survivors, alternatives to resource intensive, medically focussed models of follow-up care are required, and supported self-management has been suggested as beneficial for cancer survivors with stable disease [34]. This evaluation of a supported self-management programme for men with prostate cancer will provide useful information for management of this particular group, but will also add to the literature on alternatives to clinic based follow-up care which will be of relevance to other groups of cancer survivors across the globe.

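### Satisfaction and health service use have no T0 value, and the main regression names no patient-reported baseline score to stand in for it

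*Protocol article*

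**What the plan says.** Table 1 of the protocol article places health service use and satisfaction under "Outcome measures at T1 and T2". The text below it confirms the timing: "questions about health service use and satisfaction with follow-up care are included in the T1 and T2 questionnaires". The other patient-reported measures have a baseline; the same section states that "unmet needs, psychological wellbeing, worry about cancer recurrence, activation for self-management, and general health behaviours are being collected at T0, T1 and T2", and Table 1 lists EQ-5D-5L, EPIC-26 and FACT-G at T0 as well.

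The Data analysis section sets one rule for all outcomes, with one model fitted at 4 months and another at 8 months. Each model is specified as "controlling for study site, the outcome in question if available at T0, and baseline co-variates including age". The list continues with "type of treatment, educational attainment, time since diagnosis, domestic status, co-morbidity, employment status, and ethnic status". The next sentence adds: "If other factors differ between groups at baseline, additional controlled analyses will be carried out". The section also says that the groups will be compared at T0 on clinical and demographic characteristics and on outcome scores.

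The Discussion acknowledges that the comparator is not randomised and answers that "the inclusion of a baseline measurement helps to address this issue, allowing for statistical adjustment of known confounders".

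**The concern.** In a before-and-after cohort comparison, most of the protection against confounding comes from the baseline score. For satisfaction and service use the rule supplies none by name: the own-score term is absent, and every named covariate is demographic or clinical.

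There is a specific reason to expect imbalance. Under The Programme, men enter the new service only after PSA criteria are met and clinician and patient agree that the man's function and emotional state suit self-management. Comparator group and Eligibility state no such test for the earlier cohort. Function and distress are what FACT-G, GHQ-12, EQ-5D-5L and EPIC-26 record at T0. Co-morbidity and treatment type capture them only in part.

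Better-functioning, less distressed men would plausibly be more satisfied and use fewer services whichever service they receive. Such a difference could be read as a Programme effect on acceptability, a central question when clinic visits are replaced, or on service use, from which part of the costs is built.

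**Working it through.** **Reproducing the plan's figure.** Inputs from Sample size calculation: effect 0.3 (read as SD units), 90% power, two-sided. Alpha is not stated there, so 0.05 is assumed. The normal formula gives 234 per group and the t-test 234.5, rounded up to 235, which agrees with the stated 235. With 20% loss, 235 / 0.80 = 294, consistent with about 300 recruited. The sample size is sound and is not at issue.

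**Which terms remain in the two models.**
- Site: present.
- Own T0 score: absent, because it was not collected.
- Age, treatment, time since diagnosis, co-morbidity and the other named covariates: present.
- Any T0 patient-reported score: not named. It is possible only through the word that leaves the list open, or through the conditional extra analyses.

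**Illustrating the size.** The documents give neither a T0 imbalance nor a correlation, so both are assumed. Both must be read as what remains after the named covariates are adjusted for.
- Bias in SD units = partial correlation of the omitted T0 score with the outcome × residual T0 group difference in SD.
- Evaluable men per group = 300 × 0.80 = 240, so SE = sqrt(2/240) = 0.0913 SD.
- Rejection rate with no true effect = Φ(bias/SE − 1.96) + Φ(−bias/SE − 1.96).

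Bias in SD, with true type I error in brackets:

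| Partial correlation | Difference 0.1 SD | Difference 0.2 SD | Difference 0.3 SD |
|---|---|---|---|
| 0.2 | 0.02 (5.6%) | 0.04 (7.2%) | 0.06 (10.1%) |
| 0.3 | 0.03 (6.2%) | 0.06 (10.1%) | 0.09 (16.7%) |
| 0.4 | 0.04 (7.2%) | 0.08 (14.2%) | 0.12 (26.0%) |
| 0.5 | 0.05 (8.5%) | 0.10 (19.5%) | 0.15 (37.6%) |

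Worked cell: 0.4 × 0.2 = 0.08; 0.08 / 0.0913 = 0.876; Φ(−1.084) + Φ(−2.836) = 0.142. Against the 0.3 target, the bias runs from 0.02/0.3 = 7% to 0.15/0.3 = 50%. Service-use counts may be skewed, so for them the SD scale is only a guide.

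**How far the conditional clause protects.** No criterion for a difference is given. If it means p < 0.05 (assumed), then with 300 per group SE = sqrt(2/300) = 0.0816. A true T0 difference of 0.1 SD is flagged 23% of the time, 0.15 SD 45%, 0.2 SD 69% and 0.3 SD 96%.

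**Effect of the fix on precision.** With the T0 score in the model, the residual SD is sqrt(1 − r²). Power at 240 per group then moves from 90.8% to between 91.8% (r = 0.2) and 96.7% (r = 0.5).

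**The case against.** The strongest reply is that the safeguard sits in the next sentence. The groups are to be compared on T0 outcome scores, and a difference leads to further adjusted analyses. A reader might infer from the rule that T0 scores can never be used for these outcomes, or that any T0 difference passes unadjusted into the satisfaction contrast. The text supports neither reading: the list is open, the clause exists, and by the calculation above the imbalances behind the largest error rates are those most likely to be noticed. What remains is that the clause depends on the observed data, has no threshold and leaves the main model unchanged.

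A reader might also see a contradiction with the Discussion. There is none. That passage speaks of adjusting for known confounders, not of an own-score baseline for every outcome, and it concedes that attribution is weakened.

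Further, the article condenses a pre-specified analysis plan that is not shown and may already name such covariates. That is a fair limit. Still, the article does state a rule for every outcome and foresees a missing T0 value, yet names no substitute. Finally, only two secondary measures are touched: unmet need has its own T0 score, and the QALY regression controls for baseline utility.

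**Conclusion.** The point holds as a limited one. For satisfaction and service use, the main 4- and 8-month models contain no named patient-reported baseline score, in a non-randomised comparison where the entry criteria make differences in function and distress plausible. T0 scores might enter through the open list or the conditional analyses, but nothing commits to it. Confounding of these two contrasts is therefore possible and partly avoidable; it is not shown to have occurred.

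The range in the table, about 6% to 38% true type I error, is a conditional illustration. It rests on assumed residual imbalance and partial correlation, and takes the main model with no T0 score in it. It should not be quoted as the trial's error rate. It is also possible that comparator men were screened for suitability in a way the article does not state; the study-flow figure is not shown. The primary outcome and the sample size are unaffected.

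**What to change.** For any outcome not measured at T0, pre-specify in the main 4- and 8-month models a small set of related T0 scores, for example CaSUN unmet need plus one function or distress score such as FACT-G or GHQ-12. Include them regardless of observed imbalance. State how missing T0 items will be handled. Report the satisfaction and service-use results as comparisons without own-baseline control, and limit the Discussion's reliance on baseline measurement accordingly for these two outcomes.

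The cost is small: a sentence in the plan and no new data, since the baseline questionnaire is returned with the consent form. The planned sample size does not change and precision should improve somewhat. The main burden is missing T0 items, which would lose some men unless imputed. Confounding by factors not captured at T0 would remain.

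### Age is split in two for the subgroup interaction test although it is available as a continuous variable; modelling it continuously would make an exploratory analysis more precise at almost no cost

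*Protocol article*

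**What the plan says.** The last paragraph of the Data analysis section (Evaluation of effectiveness, protocol article) sets out the search for subgroups in four steps.

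- It names the factors: "separate regression analyses will be conducted for older versus younger men, men with and without co-morbidities, and men with higher and lower levels of deprivation".
- It places the work inside regression modelling and fixes the form of the modifier: "Interaction terms between each specified dichotomous factor (indicating subgroups) and the Programme versus standard care factor will be examined".
- It sets a rule for looking inside the subgroups: "Where interaction terms achieve statistical significance (at the 5% level), we will examine separate Programme versus comparator group estimates for each subgroup".
- It limits the standing of the results: "All subgroups analyses will be considered exploratory in nature".

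Table 1 lists date of birth among the demographic characteristics, and the regression models already include age as a covariate. No measure of deprivation is described in the article. The cut-points are not given either, but they may stand in the separate analysis plan that the section mentions, so their absence is not part of this point.

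**The concern.** Cutting a measured variable in two before testing whether the effect varies with it treats all men on one side of the cut as alike, and treats men just either side of it as different. If the Programme effect changes gradually with age, the two-group interaction is a noisier measure of that change than a slope is. The article fixes the two-group form for every factor, so the analysis gives up precision that the recorded data could supply.

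A second, smaller matter is wording. The sentence announcing separate regressions carries no condition, while the later sentence looks at separate estimates only after a significant interaction. An analyst could take the former as an instruction to fit a model within each subgroup in every case. That invites comparing a significant result in one subgroup with a non-significant one in the other, which is not a test of effect modification.

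At stake is how much the subgroup analysis can say about which men benefit. The main comparison is not affected.

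**Working it through.** **Inputs from the Sample size calculation section.** "The sample size was calculated to achieve at least 90% power in two sided tests", for an effect of 0.3 or more, read here as a standardised difference with outcome SD 1. "This would require a sample of 235 participants per group", so 470 men in all. Loss to follow-up is 20%. The 5% two-sided level is stated for the interaction test and assumed for the sample size.

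**The plan's own figure.** n per group = 2 × (1.96 + 1.2816)² / 0.3² = 2 × 10.51 / 0.09 = 233.5, so 234. The t-test version gives 234.5, so 235. Power at 235 per group is 90.2%. Allowing for loss, 235 / 0.8 = 293.75, so 294, or around 300 per arm. The stated size reproduces.

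**Assumptions for the interaction, none given in the document.** The modifier is normal, the cut is at the median, modification is linear, the outcome is continuous, and there is no covariate adjustment.

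**Information kept by a split.** For a normal modifier cut at quantile q, the share kept is φ(z_q)² / [q(1 − q)]. At the median this is 2/π = 0.637, a loss of 36.3%. The loss is 37.8% at 40/60, 42.4% at 30/70 and 51.0% at 20/80. A uniform modifier cut at its median keeps 75%, a loss of 25%.

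**Split modifier.** Each half holds 117.5 men per group. The interaction SE is √(2/117.5 + 2/117.5) = 0.1845 SD, twice the main-effect SE of √(2/235) = 0.0923. For a 0.3 SD difference between halves, 0.3 / 0.1845 = 1.626 and power = Φ(1.626 − 1.96) = 36.9%.

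**Continuous modifier.** The means of the two halves of a standard normal variable differ by 2√(2/π) = 1.596 SD. A 0.3 SD difference in effect between halves therefore corresponds to a slope of 0.3 / 1.596 = 0.188 per SD of the modifier. The slope's SE is 2/√470 = 0.0923. Then 0.188 / 0.0923 = 2.04 and power = Φ(2.04 − 1.96) = 53.1%. A simulation of 3,000 runs gave 35.4% (split) and 52.6% (continuous).

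| Difference in effect between halves | Power, median split | Power, continuous |
|---|---|---|
| 0.3 SD | 36.9% | 53.1% |
| 0.4 SD | 58.2% | 77.6% |
| 0.5 SD | 77.3% | 92.5% |
| 0.6 SD | 90.2% | 98.3% |

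**Difference detectable with 80% power.** Split: (1.96 + 0.8416) × 0.1845 = 0.52 SD. Continuous: 2.8016 × 0.0923 = 0.2585 per SD, and 0.2585 × 1.596 = 0.41 SD.

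**Precision of the split analysis.** The 95% CI half-width is 1.96 × 0.1845 = 0.36 SD.

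**Effect of adjusting for the baseline outcome.** If baseline and follow-up correlate at ρ (assumed 0.5 to 0.7), each SE is multiplied by √(1 − ρ²), that is 0.866 to 0.714. The split SE falls to 0.160 to 0.132, and power at 0.3 SD rises to about 47% to 62%. The continuous SE falls to 0.0799 to 0.0659; 0.188 divided by these is 2.35 to 2.85, and power is about 65% to 81%. The levels rise, and the gap between the two forms remains.

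**The case against.** The strongest reply is that the subgroup work is a closing, exploratory step. The Design section lists three aims (effectiveness, costs, implementation), and finding responsive subgroups is not among them. The declared exploratory status caps the harm, and that stands.

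It can also be said that two groups answer the question of distinct subgroups directly, and that a linear interaction can miss a threshold effect. This has some force. It is a reason to check the shape with a spline, but no reason to rely on a cut alone.

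Several stronger readings are tempting, and the document does not support them.

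- A reader might infer that the split makes a null interaction uninformative. It does not: the interval of about ±0.36 SD can exclude large interactions, and power is 90% at 0.6 SD. Most of the weakness comes from sizing the study for the main effect, which doubles the SE for an interaction between equal halves however the factor arose. Continuous coding still reaches only 53% at 0.3 SD.
- A reader might infer that the 5% rule weakens the interaction test. The rule applies after that test and cannot change its power. Testing the interaction before looking within subgroups is a recognised safeguard.
- A reader might infer that results will be withheld unless significant. The text governs what is examined and is silent on what is reported, and the interaction terms are examined in every case.
- A reader might see a contradiction between the separate regressions and the interaction rule. The former can be read as one regression per factor, with the following sentences explaining how. The wording is ambiguous, no more.
- A reader might carry the loss over to deprivation. No deprivation measure is described, so no loss can be calculated for it. Co-morbidity is named as a with-or-without factor, and the point does not apply to it.

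**Conclusion.** The point holds as a modest improvement to a stated method. The article fixes a two-group form for age although the data allow a continuous one. Under a normal modifier, a median split and linear modification, this loses about 36% of the information on the interaction, within a range of about 25% to 51% by distribution and cut-point. At 235 per group and before covariate adjustment, power for a 0.3 SD difference between halves falls from 53% to 37%, and the difference detectable with 80% power rises from 0.41 to 0.52 SD. Adjustment for baseline would raise both power figures, by an amount the document does not allow one to fix. The consequence is small and the primary conclusion of the evaluation does not depend on it. The sentence on separate regressions needs only to be aligned with the interaction approach.

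**What to change.** - Fit the Programme by age interaction with age continuous and linear, using a simple spline as a check for non-linearity. Do the same for deprivation if it is recorded on a graded scale. Leave co-morbidity as a with-or-without factor.
- Report each interaction estimate with its 95% CI whatever its p-value.
- Reword the sentence on separate regressions so that subgroup effects are derived from the interaction model, and present predicted Programme effects at a few chosen ages.

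The cost is a change of wording in the analysis section: no new data and no more participants, and the analyses stay exploratory. The downside is that a continuous form assumes a shape for the modification, and the results are slightly less simple to present than two groups.
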